**Question prompt lists**
Question prompt lists are prepared lists of questions that are designed to enable patients to identify questions they wish to ask the health care professional.Question prompt lists are embedded within the content areas of the SUCCESS (Supporting Culturally and Linguistically Diverse CKD Patients to Engage in Shared Decision-Making Successfully) app (eg, there is a question prompt list related to taking medications).Users are able to choose from a predefined list or write their own questions, which are saved in the app dashboard for use in upcoming health care consultations.
**Volitional help sheets**
A volitional help sheet is a tool designed to enable the construction of effective implementation intentions in which participants are asked to link in memory temptations (ie, difficult situations that result in urges to engage in a specific behavior) with processes of change (ie, means by which behavior is changed or sustained).Volitional help sheets are embedded within each content area of the SUCCESS app. For example, participants can create a volitional help sheet to make a plan to drink less fluids. Plans are saved in the app dashboard for future use.
**Videos**
Animated videos are available to build skills in the following areas:Health care communication (eg, “Talking to your health care team”)Shared decision-making (eg, “Making decisions”)Critical appraisal of online information (eg, “Can I trust this health information?”).
**Quizzes**
Content-specific quizzes are embedded into the app to encourage feedback and learning through the use of targeted questions separated by levels of difficulty.Users receive feedback and further information about the content of the quiz based on their understanding.

#### Public and Patient Involvement

A key strength of the development of the SUCCESS app was the combined effort of clinicians, health literacy experts, and consumers in the app development process. One consumer and a representative of Kidney Health Australia, the largest consumer advocacy organization for people with kidney disease, were part of the development team and provided valuable feedback regarding app content and usability. Further to this, the app was iteratively improved based on consumer feedback during the development the feasibility testing phases leading up to this trial. As part of this trial, we will continue to seek further feedback from participants on the SUCCESS app and make improvements, if required, after completion of the trial.

### Study Setting

This study will be conducted across six local health districts charged with delivery of health care within the public sector in the Greater Sydney region—Sydney, Northern Sydney, Western Sydney, South Western Sydney, Nepean Blue Mountains, and Illawarra Shoalhaven—including six university teaching hospitals and six community dialysis centers. The Greater Sydney region includes 4,823,991 people (64.5% of the New South Wales population; 20% of the Australian population), of which 38% speak a language other than English at home [19]. The research sites were purposively selected to include broad geographical coverage across Sydney as well as socioeconomic and cultural diversity.

### Study Population

The target population for this study are adults aged 18 years or over who are receiving dialysis, including those receiving in-center hemodialysis, either in the hospital or community hemodialysis centers; home hemodialysis; and peritoneal dialysis. Only participants who have the ability to speak English sufficiently well to provide informed consent will be recruited. We intend to translate and culturally adapt the app into other languages to further expand the diversity of future app users. Participants lacking the cognitive capacity to consent as determined by the nursing staff will be excluded.

### Recruitment

Eligible participants will be identified by their health care providers and approached by the research team either in person during dialysis sessions or clinic visits or via telephone, email, or a letter of invitation; at this time, they will be provided with information about the study. Participants will be entered into the study after written consent is obtained on paper or via REDCap (Research Electronic Data Capture) and after eligibility criteria are met.

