#### Dialysis at In-Center Units

It is standard practice for patients on hemodialysis at the in-center units to receive dialysis treatment three times a week. Patients receiving in-center dialysis always attend on the same days: either Mondays, Wednesdays, and Fridays or Tuesdays, Thursdays, and Saturdays. Therefore, a pragmatic approach will be used at each center by randomizing patients according to their pattern of attendance. Depending on the center, all participants attending Monday, Wednesday, and Friday will be assigned to the same study intervention group, and those attending Tuesday, Thursday, and Saturday will be assigned to the alternate study intervention group.

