### Study Outcomes

Once informed consent is obtained, baseline measures will be collected, including demographics, dialysis history, cognition level, and health and digital literacy status (Table 1 [20-30]). Our primary outcomes are health literacy, shared decision-making, and rates of unscheduled health encounters; these will be assessed at 3, 6, and 12 months of app usage (Table 1). Secondary outcomes include patient-reported outcomes and clinical outcomes; these will also be assessed at 3, 6, and 12 months of app usage (Table 1).

**Table 1 table1:** Measurements collected throughout the trial.

Measure and description			Timepoint (month)							
			0		3		6		12	

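### The day-pattern rule makes an in-center patient's arm predictable before approach and consent once a center's assignment is known, and no stated recruitment step offsets this

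*Protocol article*

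**What the plan says.** Protocol article, Dialysis at In-Center Units: the unit of allocation is the attendance pattern within a center. The text states that "all participants attending Monday, Wednesday, and Friday will be assigned to the same study intervention group" and that "those attending Tuesday, Thursday, and Saturday will be assigned to the alternate study intervention group". It also says "Patients receiving in-center dialysis always attend on the same days", so a patient's pattern is stable and visible to staff.

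Recruitment: "Eligible participants will be identified by their health care providers and approached by the research team". The approach may be made "either in person during dialysis sessions or clinic visits or via telephone, email, or a letter of invitation". Entry is individual: "Participants will be entered into the study after written consent is obtained on paper or via REDCap".

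Study Population adds a staff judgment to eligibility: "Participants lacking the cognitive capacity to consent as determined by the nursing staff will be excluded".

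Study Outcomes places baseline after consent: "Once informed consent is obtained, baseline measures will be collected".

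Dialysis at Home describes a call to an outside trials center for allocation. Dialysis at In-Center Units describes no such step.

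Data Analysis names study arm, center (random effect) and home versus in-center care as model terms. It names no baseline score or other prognostic covariate.

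**The concern.** Concealment means that whoever decides a patient's entry cannot foresee the arm. A fixed day pattern combined with one assignment per center removes that protection for every in-center patient recruited after the assignment is known. Even an unannounced assignment is disclosed by the first patient on a pattern who receives the app, because the other pattern must be the alternate arm.

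The intervention is a smartphone app and the comparator is usual care alone, so two routes to imbalance are plausible. Providers could identify phone-capable or health-literate patients more readily on app days. Patients on usual-care days could see less reason to consent. Either would make the enrolled groups differ before treatment. The HLQ domains and the Decision Self-Efficacy Scale are self-reported primary outcomes, and health literacy is close to the trait on which selection would act. A larger sample does not reduce such a bias.

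**Working it through.** **Step 1: what the text fixes.** Set side by side, the sections give this sequence for in-center patients:

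- Pattern known to staff: always, since attendance days are fixed.
- Arm given the pattern: determined by one assignment per center, with the two patterns in opposite arms.
- Identification: by providers. Approach: by the research team, possibly at the dialysis session. Capacity to consent: judged by nursing staff.
- Entry: individual, on consent.
- Date on which the center's assignment is made or released: not stated. The study-flow figure is not available in the text reviewed.

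The arm is therefore predictable for every in-center patient approached after release, and for every such patient approached after the first app user is seen. It is unpredictable only for those consented before both events. The article states no step that places consent before release, no recruiter unaware of the allocation, and no requirement to approach every eligible patient.

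**Step 2: the plan's own power figure.** Inputs from Sample Size: N = 384, 20% loss, difference 0.25, two-sided 5%, SD 0.60 or 0.75.

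- n per arm = 384 × 0.8 / 2 = 153.6.
- SE = SD × √(2/n): 0.60 × 0.1141 = 0.0685, and 0.75 × 0.1141 = 0.0856.
- Power ≈ Φ(0.25/SE − 1.96): Φ(1.69) = 95.5% and Φ(0.96) = 83.2%.

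Both meet the stated bounds (above 90% and at least 80%). The sample-size statement is not what is at issue here.

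**Step 3: how large a bias could matter.** The documents give neither the size of any selection nor the in-center share, so both are assumed. Let b be the selection-induced HLQ difference between in-center arms and s the in-center share, with home patients unbiased and the same arm ratio in both groups. Then the overall bias is b × s, and its share of the target is b × s / 0.25. With no true effect, the two-sided 5% test rejects with probability 1 − Φ(1.96 − b·s/SE) + Φ(−1.96 − b·s/SE). Clustering and baseline adjustment are ignored.

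| b (assumed) | s (assumed) | Bias b × s | Share of 0.25 | Rejection, SD 0.60 | Rejection, SD 0.75 |
|---|---|---|---|---|---|
| 0.05 | 50% | 0.025 | 10% | 6.5% | 6.0% |
| 0.05 | 75% | 0.0375 | 15% | 8.5% | 7.2% |
| 0.05 | 100% | 0.05 | 20% | 11.3% | 9.0% |
| 0.10 | 50% | 0.05 | 20% | 11.3% | 9.0% |
| 0.10 | 75% | 0.075 | 30% | 19.5% | 14.2% |
| 0.10 | 100% | 0.10 | 40% | 30.9% | 21.5% |

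In SD units the assumed shifts are modest: 0.05/0.75 = 0.07 to 0.10/0.60 = 0.17. The table shows sensitivity to the assumptions and does not estimate what will happen.

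**Step 4: whether the stated models would remove it.** The center effect compares patients within a center, but the two patterns within a center are the two arms, so a difference in who enrolled remains inside that comparison. The home versus in-center term does not touch it either.

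**The case against.** The strongest reply is that bias requires the assignment to be known before patients are identified and consented, and the article does not say that it is. A condensed article may leave the order of release and consent to the full protocol. If all patients at a center consented before release, the risk would largely go. This stands as a limit on the claim. It does not remove the point, because individual entry under a visible, deterministic rule is what the article itself fixes. Patients who enter after the first app user is seen are not concealed, whatever was announced.

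Three stronger readings are tempting, and the documents do not support them:

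- A reader might infer that staff choose among eligible patients. The text says that providers identify eligible patients and researchers approach them, which is compatible with listing everyone.
- A reader might infer that baseline scores are reported with the arm known. The text says only that baseline follows consent.
- A reader might take 20 to 40% of the target as the expected bias. That range rests on an assumed shift and on every participant being in-center.

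Other mitigating points are fair. Randomization, Overview gives a sound reason for day-pattern allocation: patients share a room for hours, three times a week, and contamination is a real threat. Table 1 collects HLQ, decision self-efficacy, health literacy and digital literacy at baseline, so selection on those traits would be partly visible and open to adjustment. Motivation and willingness are not among the measures listed. Unscheduled encounters are verified against medical records and depend less on self-report.

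**Conclusion.** The point holds as an exposure to recruitment bias in the in-center comparison. It does not extend to home patients, who are allocated individually through a third party, and it does not show that bias has occurred or that any site recruited selectively.

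The size is unknown. Under assumed in-center shifts of 0.05 to 0.10 HLQ units, the overall bias would be 10 to 20% of the 0.25-unit target at a 50% in-center share, rising to 20 to 40% only if all participants are in-center. Confidence is medium, because the timing of release is unstated. The change is still worth making: lost concealment cannot be restored at analysis, and the remedy keeps the contamination-limiting design.

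**What to change.** 1. State, for each center, when the day-pattern assignment is made and released relative to consent.
2. At centers not yet allocated, list eligible patients on both patterns from the dialysis roster and complete consent and baseline for that wave. Only then release the allocation.
3. Where the allocation is already known, and for patients who become eligible later, approach every eligible patient on the roster for both patterns. Keep a log and report numbers eligible, approached and consented by day pattern.
4. Adjust the HLQ and decision self-efficacy models for the baseline score and for the health literacy and digital literacy measures already collected.

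Cost: early consenters at a center wait for the app, and there is some roster and log work. Results reports recruitment under way at nine sites, so step 2 may reach few centers and step 3 may carry most of the weight. Differential consent remains possible wherever the allocation is already known; the counts let readers judge it, and the adjustment removes only the part that runs through measured traits.

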### Randomization

#### Overview

Participants will be randomly allocated to either the SUCCESS app plus usual care (intervention) or usual care alone (control). Participants who are randomized to the intervention will be invited to use the SUCCESS app for a maximum of 12 months. Participants will be instructed to engage with the app *ad libitum* and will also receive monthly reminders to use the app via push notifications.

We will not randomize all participants individually due to the risk of intervention contamination, where the intervention is experienced by control group members as well as those allocated to the intervention group. This is possible because participants in the control and intervention arms may undergo dialysis in the same room three times each week for several hours. Instead, a two-tier pragmatic approach will be used to randomize participants depending on whether they are undergoing dialysis at home or receiving dialysis at the in-center (ie, satellite) dialysis units. Our planned approach will minimize contamination and allow for within-center comparisons.

#### Dialysis at In-Center Units

It is standard practice for patients on hemodialysis at the in-center units to receive dialysis treatment three times a week. Patients receiving in-center dialysis always attend on the same days: either Mondays, Wednesdays, and Fridays or Tuesdays, Thursdays, and Saturdays. Therefore, a pragmatic approach will be used at each center by randomizing patients according to their pattern of attendance. Depending on the center, all participants attending Monday, Wednesday, and Friday will be assigned to the same study intervention group, and those attending Tuesday, Thursday, and Saturday will be assigned to the alternate study intervention group.

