**Methods:**

We designed a multicenter pragmatic randomized controlled trial to compare the SUCCESS app plus usual care (intervention) to usual care alone (control). A total of 384 participants receiving in-center or home-based hemodialysis or peritoneal dialysis will be recruited from six local health districts in the Greater Sydney region, New South Wales, Australia. To avoid intervention contamination, a pragmatic randomization approach will be used for participants undergoing in-center dialysis, in which randomization will be based on the days they receive hemodialysis and by center (ie, Monday, Wednesday, and Friday or Tuesday, Thursday, and Saturday). Participants undergoing home-based dialysis will be individually randomized centrally using simple randomization and two stratification factors: language spoken at home and research site. Consenting participants will be invited to use the SUCCESS app for 12 months. The primary endpoints, which will be assessed after 3, 6, and 12 months of app usage, are health literacy skills, evaluated using the Health Literacy Questionnaire; decision self-efficacy, evaluated using the Decision Self-Efficacy Scale; and rates of unscheduled health encounters. Secondary outcomes include patient-reported outcomes (ie, quality of life, evaluated with the 5-level EQ-5D; knowledge; confidence; health behavior; and self-management) and clinical outcomes (ie, symptom burden, evaluated with the Palliative care Outcome Scale–Renal; nutritional status, evaluated with the Patient-Generated Subjective Global Assessment; and intradialytic weight gain). App engagement will be determined via app analytics. All analyses will be undertaken using an intention-to-treat approach comparing the intervention and usual care arms.

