#### Dialysis at Home

Participants will be randomized individually using minimization and two stratification factors: the language spoken at home and the research site. An interactive voice response system will be used for randomization; this allows for research staff to call a third party—the National Health Medical Research Council Clinical Trials Centre—which allocates the randomization order.

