**Primary outcomes: patient-reported outcomes**										
	Health literacy skills: the HLQ^e^, a multidimensional tool that measures health literacy across nine distinct conceptual domains, will be used. The median reliability of the HLQ domains is 0.88, with a range from 0.77 to 0.90 [26]. For the purpose of this study, we have selected three to domains to explore: Domain 2: have sufficient information to manage my health Domain 6: ability to actively engage with health care providers Domain 9: understand health information well enough to know what to do. Domain 2 assesses the strength of a participant’s agreement with the statement on a 4-point ordinal scale, ranging from 1 (“strongly disagree”) to 4 (“strongly agree”); domains 6 and 9 assess a participant’s perceived ease in task completion on a 5-point ordinal scale, ranging from 1 (“always difficult”) to 5 (“very easy”).	✓		✓		✓				✓
	Decision self-efficacy: the Decision Self-Efficacy Scale [23] measures self-confidence or belief in one’s ability to make decisions, including participation in shared decision-making. This item consists of 11 questions where participants rate their confidence engaging in decision-making behaviors, such as “Getting the facts about the medication choices available.” Items are rated on a 5-point ordinal scale ranging from 1 (“not at all confident”) to 5 (“very confident”).	✓		✓		✓				✓
	Rates of unscheduled health encounters: this includes unexpected hospital and emergency visits and unscheduled dialysis events in the past 3 months as reported by participants; this is also verified by extracting this information from electronic medical records.			✓		✓				✓

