### Data Analysis

#### Overview

Analysis of data will occur using an intention-to-treat approach and will compare the intervention and usual care arms. For continuous and binary outcomes, linear and logistic regression models will be used, respectively, with study arm as a covariate. All models will also be adjusted for center using a random effect, and the type of patient (ie, receiving home-based or in-center care) will be adjusted for using a covariate.

Qualitative data will be analyzed using the Framework approach to thematic analysis [31]. Framework analysis is a matrix-based approach with columns depicting themes and rows listing the cases, enabling the relationship between themes and cases to be explored. The first step involves familiarization with the data, where one or two researchers will review the transcript and, using an inductive approach, they will then develop a list of emerging topics and salient themes. These initial impressions will form the basis of the coding framework. Then, additional researchers will independently read a subset of transcripts and review the framework, which will further be revised with continuous discussion if needed. One researcher will then code all the interviews into the final framework, of which a random subset (10%) will be double coded by an additional researcher to ensure rigor. Similarities or differences will be discussed and reassessed. Microsoft Excel will be used to summarize the themes and supporting quotes from each transcript in the framework. Prominent themes arising from the framework will be identified and discussed in-depth with the research team.

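### In-center participants are allocated as whole day-pattern groups, but the analysis model has no term for those groups, so differences between them can enter the app effect and its standard error is too small

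*Protocol article*

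**What the plan says.** The Protocol article, under Dialysis at In-Center Units, allocates by attendance pattern. At a given center "all participants attending Monday, Wednesday, and Friday will be assigned to the same study intervention group". Patients on the other attendance pattern at that center get the opposite arm. The same section says that the assignment depends on the center, and the abstract says that "randomization will be based on the days they receive hemodialysis and by center". So the pattern that receives the app is set center by center and is not one fixed pattern for the whole trial. Home-based participants are handled differently: "Participants will be randomized individually using minimization and two stratification factors" (Dialysis at Home).

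The Data Analysis overview gives the model: "linear and logistic regression models will be used, respectively, with study arm as a covariate". It then adds that "All models will also be adjusted for center using a random effect", together with a covariate for home-based or in-center care. It names no term for day pattern and none for the day-pattern group within a center.

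**The concern.** Within any in-center unit, app versus control is the same contrast as one day pattern versus the other. Arm and day pattern can be told apart only across units, through the mix of which pattern received the app where. A center effect shifts both day groups of a unit equally, so it cannot remove a difference between them.

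Two kinds of difference matter. One is common to all centers, for instance if the kind of patient who attends differs systematically between the two patterns. The other belongs to a particular group at a particular center, such as its own staff or case mix. The first can leave a remainder in the estimated app effect. The second is variation between allocation units that the model counts as variation between individuals, so the standard error is too small. At stake are the false-positive rate of the primary comparisons and the stated power.

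**Working it through.** **Inputs from the Protocol article.** Under Sample Size: 384 participants, 20% loss, difference 0.25 HLQ units, SD 0.60 or 0.75, two-sided 5%. Under Study Setting: six hospitals and six community centers, hence 12 units. Under Results: recruitment begun at nine sites. The article gives no center-by-day intraclass correlation (ICC), no in-center share, no day-group difference and no description of how the per-center draw is made. These are assumed below.

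**Stated power.** 384 × 0.8 / 2 = 153.6 per arm. The standard error is SD × √(2/153.6), which is 0.0685 at SD 0.60 and 0.0856 at SD 0.75. Power is 95.5% and 83.2%, which agrees with the stated figures of more than 90% and at least 80%. It treats every participant as individually randomized.

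**Difference common to all centers.** Let s = (units with Monday-Wednesday-Friday on the app − units with Tuesday-Thursday-Saturday on the app) / units. With units of equal size, a fraction s of a common day difference stays in the in-center app effect. With an independent fair coin per unit (assumption), s has mean 0. The mean of |s| is 0.226 with 12 units and 0.273 with 9. With 12 units the chance of each split is:

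- 6:6, 22.6%
- 7:5, 38.7%
- 8:4, 24.2%
- 9:3 or worse, 14.6%

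The bias in the overall effect is day difference × s × in-center share. Assume a share of 75% and a day difference of 0.10 to 0.20 HLQ units:

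- 7:5 (s = 2/12): 0.0125 to 0.025 units, which is 5% to 10% of 0.25. Two-sided error is 5.2% to 6.5% across both SDs.
- 9:3 (s = 6/12): 0.0375 to 0.075 units, which is 15% to 30% of 0.25. Error is 7% to 14% at SD 0.75 and 8.5% to 19.5% at SD 0.60.
- Averaged over all splits of 12 units: 5.7% to 6.2% for a difference of 0.10, and 8.0% to 9.8% for 0.20.

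Error here is P(|Z + bias/SE| > 1.96).

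**Group-specific differences.** The design effect for in-center participants is 1 + (m − 1) × ICC, with m the number analysed per center-by-day group. With all 307 in-center, m is about 12.8 (12 units) or 17.1 (9 units). Type I error was simulated for a model with arm and center only, no common day difference and a random per-center draw. Groups were rounded to 13 and 17.

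| ICC | 12 units | 9 units |
|---|---|---|
| 0 | 5.1% | 4.6% |
| 0.01 | 6.4% | 6.8% |
| 0.02 | 8.4% | 9.0% |
| 0.05 | 12.2% | 14.6% |

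The approximation 2 × [1 − Φ(1.96/√design effect)] agrees. At ICC 0.05 the design effects are 1.59 and 1.80, which give 12.0% and 14.4%.

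**Power once the groups are modelled.** The design effect is applied to in-center participants only. Each cell gives SD 0.60 / SD 0.75.

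| ICC | 12 units, 75% in-center | 9 units, all in-center |
|---|---|---|
| 0.01 | 94% / 81% | 92% / 77% |
| 0.02 | 93% / 79% | 89% / 72% |
| 0.05 | 90% / 73% | 78% / 59% |

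These use normal critical values, so small-sample degrees of freedom would lower them a little further.

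**The case against.** A reader might infer that every difference between the day groups becomes bias in the app effect. The documents do not support that. The pattern receiving the app is set per center. If that is random, a common difference has opposite signs in different centers and zero expected bias, and an even split of equal-sized units removes it. Home-based participants are unaffected.

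A reader might also point to where the long interdialytic gap falls, because unscheduled encounters are a primary outcome. Friday to Monday and Saturday to Tuesday are equally long and recur equally often over a 3-month recall period, so the article gives no ground for expecting a difference on that account.

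The larger error rates at 9:3 depend on an uneven split and on a day difference of 0.10 to 0.20 units, which is 40% to 80% of the 0.25 target and has no source in the article. At the more likely 6:6 or 7:5 split (61.3% together) the effect is small.

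Finally, this is a condensed article, and a separate analysis plan may add terms. That carries some weight for a further covariate. It carries less here, because the article names the adjustment for all models and that adjustment leaves out the unit of allocation. The group-specific variation needs neither an uneven split nor a common day difference to raise the error rate.

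**Conclusion.** The point holds. Arm coincides with day pattern within each in-center unit, and the stated model cannot absorb differences between the two day groups of a center. The main consequence is a standard error that is too small: two-sided error of about 6% to 15% for an assumed ICC of 0.01 to 0.05 with all participants in-center, and less if a sizeable share dialyze at home. The second consequence is a chance remainder of any common day difference, on average 0.23 (12 units) or 0.27 (9 units) of it in the in-center effect under unrestricted coin flips. If the draw was restricted to be balanced, this second part largely disappears. If it was not random, it could be larger. The direction of any distortion cannot be known in advance. The margin at SD 0.75 is thin: 83.2% against a stated 80%, which an ICC of 0.01 takes to 77% to 79% if all participants are in-center.

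**What to change.** In the Data Analysis overview:

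- Add a random effect for the center-by-day-pattern group, for in-center participants only, and test the arm effect with small-sample degrees of freedom.
- Replace the two-level patient-type covariate with three levels: home, in-center Monday-Wednesday-Friday, and in-center Tuesday-Thursday-Saturday. This can be estimated only if the pattern receiving the app differs between centers. It does not replace the random effect, because group-specific variation would remain unmodelled.

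If any units are still unallocated, assign them so that each pattern receives the app in half of the units, or as near to half as possible. State how the per-center draw was made, and restate power with an assumed ICC.

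Cost: both terms use information already known for every in-center participant. Intervals become somewhat wider. The variance inflation of the in-center effect from the day covariate is 1/(1 − s²), which with 12 units is 1.00 at 6:6, 1.03 at 7:5, 1.13 at 8:4 and 1.33 at 9:3. The random effect widens intervals in line with the design effects above, and that is uncertainty the present model leaves out.
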